### Recruitment and Sampling

Participants will be recruited from the community through a multipronged strategy combining online and offline dissemination. This will include social media outreach, online announcements, and dissemination of posters in colleges, workplaces, and community locations. The inclusion criteria for the study are individuals aged 18 years and older, of all genders, fluent in English or Kannada, with at least 10 years of formal education, comfortable using a smartphone, experiencing self-reported current depressive or anxiety symptoms for 2 weeks or longer, and scoring 20 or above on the Kessler Psychological Distress Scale (K10) [25]. Participants will be excluded if they are currently receiving pharmacological treatment for any mental health condition, have attended 3 or more psychotherapy or counseling sessions in the past 3 months, or are presently engaged in counseling or psychotherapy. Individuals currently using any other mental health app, or those not amenable to participating in the study as assessed in a brief telephonic interview, or those having significant suicidal ideation as determined by responses on 2 items pertaining to the frequency and controllability of suicidal thoughts in the past 1 month, will be excluded from the study.

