### Power Calculation

A sample size of 150 participants per group has been estimated based on detecting a difference in help-seeking behavior (25% vs 10%) with 80% power at a 5% significance level using G*Power 3.1, allowing for up to 33% attrition commonly observed in minimally guided digital interventions [26]. These include interventions delivered through digital platforms, which often vary widely in design and outcomes. Consequently, closely comparable studies for precise sample size estimation were difficult to identify, and the current estimate is informed by findings from studies with broadly similar characteristics [14,27].

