### Procedure

Participants will be randomized into either the intervention or control group in a 1:1 ratio, using a computer-generated randomization sequence. The randomization list will be generated by the study supervisor. Stratified randomization will be used based on age group (18-35 years and 36 years and above) and gender to ensure balance across key demographic variables.

A brief telephonic interview for eligibility screening will be conducted after all other questionnaires are completed. This call allows the researchers to clinically assess the current mental state and amenability to take part in the study process, inquire whether participants have sought consultation for any psychiatric problem in the past or recent times, and confirm willingness to participate.

Eligible participants will receive an introductory call informing them of their group allocation and guiding them on how to begin engagement with the study activities. All assessments will be conducted through an online survey, and feedback will be obtained over the phone from both groups at the end of the 4-week intervention period. A follow-up telephonic interview will be conducted 1 month after the postintervention assessment to ascertain help-seeking inclination and help-seeking behavior. The flow of the study is depicted in Figure 1.

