### Data Collection Instruments

The demographic and basic data sheet will be used to collect demographic information. In addition, the basic data sheet will include items assessing prior consultations with mental health professionals (if any), significant life events or ongoing stressors, and available sources of support during difficult times. To assess self-perceived common mental health concerns, participants will respond to an item regarding their current experience of depressive and/or anxiety symptoms. This item will inquire whether they are currently experiencing (1) persistent sadness or loss of interest in previously enjoyable activities; (2) frequent feelings of nervousness, tension, or anxiety; (3) both; or (4) none of the above. The duration of these concerns will also be captured using predefined categories ranging from less than 2 weeks to more than 6 months. Perceived severity of distress and its interference with daily functioning will be measured using a 5-point Likert-type scale, and another item will capture any current engagement in professional help-seeking. Participants will also respond to an open-ended item about the 3 self-help methods they use most frequently. Additional items rated on a 5-point Likert scale will assess the perceived usefulness of self-help strategies, self-rated perseverance in pursuing personal goals, and interest in learning self-help skills for mental health and well-being.

The K10 is a 10-item standardized measure of distress related to anxiety and depression symptoms over the past 4 weeks. It has demonstrated good psychometric properties in varied samples [25,30,31]. A total score of ≥20 indicates significant psychological distress and potential mental disorder [25]. The scores on this tool will be used to recruit eligible participants for the study (distressed nontreatment-seeking individuals). Participants who score 20 or above on K10 will be included in the study. The scores will also be used to document changes, if any, in psychological distress during the course of the study (secondary outcome).

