### Data Analysis Plan

Quantitative analyses will be conducted using SPSS Statistics (version 31.0; IBM Corp). Baseline characteristics will be summarized descriptively. Differential attrition will be examined by comparing dropout rates between groups using chi-square tests and by assessing baseline differences between completers and noncompleters using appropriate statistical tests. Sensitivity analyses will be conducted as needed based on the observed pattern of missing data.

Occurrence of professional help-seeking at the postintervention assessment and follow-up will be compared between groups using proportions, chi-square tests, and odds ratios with 95% CIs, with Cohen *h* reported as the effect size. As this behavioral outcome has no baseline variation in the nontreatment-seeking study sample, this will be treated as a completer analysis involving participants who provided postintervention assessment data.

For continuous outcomes, linear mixed-effects models will be used to estimate group, time, and group×time effects under an intention-to-treat framework. In addition, completer-only analyses will be conducted as exploratory comparisons to describe observed change among participants with complete data. A 2-sided significance level of .05 will be used.

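### The premise of no baseline variation in help-seeking is not secured by the eligibility criteria, and the unadjusted primary analysis forgoes precision that baseline data already collected could give

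*Protocol article*

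**What the plan says.** **Analysis.** The Data Analysis Plan compares the occurrence of professional help-seeking at postintervention and follow-up by proportions, a chi-square test and an odds ratio with its 95% interval. No covariate is named. It then reasons "As this behavioral outcome has no baseline variation in the nontreatment-seeking study sample" and concludes that the analysis will be restricted to completers.

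**Eligibility.** Recruitment and Sampling excludes people on current medication for a mental health condition and those who "have attended 3 or more psychotherapy or counseling sessions in the past 3 months, or are presently engaged in counseling or psychotherapy".

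**Baseline data.** Data Collection Instruments places items on earlier consultations with mental health professionals on the basic data sheet. The Procedure section has the screening call "inquire whether participants have sought consultation for any psychiatric problem in the past or recent times". The yes/no help-seeking item is given at baseline as well as at the two later assessments. The General Help-Seeking Questionnaire (GHSQ) has an item on mental health professionals, which is named as the main focus of that scale.

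**Randomisation.** The Procedure section stratifies by age group and gender, not by prior consultation.

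**The concern.** The analysis section treats the sample as uniform at baseline on the behaviour that the trial is meant to change. The recruitment section admits people with different histories of that behaviour, and two separate instruments record the history. Either the premise is wrong, or it holds only under a definition of the baseline item that the article does not give.

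Three things are at stake:

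- **Precision.** Past consultation and baseline inclination plausibly predict later consultation. A crude comparison leaves that information unused.
- **Interpretation.** A return visit by someone who had a session two months before entry counts the same as a first contact.
- **Justification.** The premise is offered as the reason for a completer analysis. A constant baseline value, even if true, is no reason to leave out randomised participants whose outcome is missing, and the Power Calculation allows for up to 33% attrition.

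**Working it through.** **1. The texts side by side**

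| Participant at entry | Eligible on these criteria? | Baseline item if it means current engagement or consultation since joining | Baseline item if it means recent or lifetime consultation |
|---|---|---|---|
| Never consulted | Yes | No | No |
| Earlier care, ended more than 3 months ago | Yes | No | No (recent) or Yes (lifetime) |
| 1 or 2 sessions in past 3 months, not engaged now | Yes | No | Yes |
| 3 or more sessions in past 3 months, or engaged now | No | not applicable | not applicable |

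The premise holds in the third column and fails in the fourth. The article does not say which column applies. After baseline, the wording of the follow-on question implies a window starting at study entry, but the baseline administration of the item has no stated window. In both columns the three eligible rows differ in consultation history.

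**2. The plan's own sample size**

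Inputs from the Power Calculation: 25% vs 10%, "with 80% power at a 5% significance level", 33% attrition. From the Data Analysis Plan: two-sided .05.

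n = [1.96·√(2·0.175·0.825) + 0.8416·√(0.25·0.75 + 0.10·0.90)]² / 0.15² = (1.0532 + 0.4434)² / 0.0225 = 99.5, so 100 per arm.

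100 / (1 - 0.33) = 149.3, so 150 per arm. The stated figure reproduces. Nothing here turns on an arithmetic error.

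**3. What adjustment for prior consultation would gain**

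The documents give neither the prevalence of prior consultation nor its association with the outcome. Assumed ranges: prevalence 10% to 50%, odds ratio 1 to 5. Simulation with 100 completers per arm, marginal rates held at 10% and 25%, 6,000 runs per setting, crude chi-square against a Cochran-Mantel-Haenszel test stratified by prior consultation:

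| Prevalence | Odds ratio | Crude power | Stratified power | Conditional treatment odds ratio |
|---|---|---|---|---|
| 10% | 1 | 81.5% | 81.1% | 3.00 |
| 10% | 5 | 82.1% | 83.4% | 3.21 |
| 20% | 1 | 82.4% | 81.8% | 3.00 |
| 20% | 5 | 81.1% | 83.6% | 3.32 |
| 30% | 3 | 81.1% | 82.7% | 3.15 |
| 30% | 5 | 81.8% | 84.9% | 3.34 |
| 50% | 5 | 81.7% | 83.8% | 3.26 |

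Over the whole grid the change is about -1 to +3 points. It exceeds simulation noise mainly at odds ratios of 3 to 5.

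**4. What adjustment for a baseline score would gain**

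The score stands for the GHSQ mental health professional item, taken as a normal variable with an assumed odds ratio per SD. Same rates and arm size, 4,000 runs per setting (Monte Carlo standard error about 0.6 points):

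| Odds ratio per SD | Crude | Adjusted, likelihood ratio | Adjusted, Wald | Conditional treatment odds ratio |
|---|---|---|---|---|
| 1.5 | 81.5% | 82.0% | 80.9% | 3.08 |
| 2.0 | 82.4% | 84.5% | 83.5% | 3.23 |
| 2.7 | 81.4% | 86.4% | 85.2% | 3.48 |

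Allowing for simulation error and the choice of test, the gain is about 0 to +6 points.

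**The case against.** **The sentence may be literally true.** It concerns the outcome, which is consultation after entry. Nobody has that at baseline, and people currently engaged in care are excluded. On this reading, consultation history is a covariate and not the baseline value of the outcome. This stands in part: the conflict with the eligibility criteria is conditional on an undefined look-back. It does not remove the need to define the item, and it does not make the participants equal in prospect.

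**The premise is not the stated reason for omitting covariates.** This stands. The article uses it to justify restricting to completers. The unadjusted comparison is simply the method that it states.

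**The crude test is valid.** This also stands. In a 1:1 randomised trial, omitting a prognostic covariate neither biases the marginal comparison nor inflates the type I error, and the confidence interval already allows for chance imbalance. Adjustment is a matter of efficiency, and a full analysis plan, not shown, may contain it.

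**A reader might infer a large loss of power.** Suppose 15% were recent consulters, 50% of whom consult again, against 8% of the others. The control rate is then 0.15·0.50 + 0.85·0.08 = 14.3%. Holding the 15-point gain (29.3% vs 14.3%), exact power at 100 per arm is 74%, against 82% for 25% vs 10%. The documents do not support this as a finding:

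- None of the three inputs is in the documents. Together they imply an odds ratio of (0.50/0.50)/(0.08/0.92) = 11.5.
- With 5% prevalence and the same rates, the control rate is 0.05·0.50 + 0.95·0.08 = 10.1%, and power is 81%.
- Holding the planned odds ratio of 3 instead of the difference gives odds of 3·0.143/0.857 = 0.501, a rate of 33.4%, and about 90% power. The direction depends on which effect scale is held.
- Covariate adjustment would not undo a higher control rate in any case.

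**Conclusion.** The point holds as a conditional inconsistency of text and a modest loss of efficiency. The premise is either contradicted by the eligibility criteria or true only under a definition that the article does not state. On either reading it gives no support for the completer restriction, and it does not show that baseline information is useless.

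The size is small: about -1 to +3 power points from prior consultation and about 0 to +6 from a baseline score. Both rest on the assumed associations above and on 100 completers per arm. The adjusted odds ratio is conditional and will be somewhat larger than the crude one (3.00 against up to about 3.5 in these settings). This is a change of estimand, not a larger effect.

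No claim of bias or inflated type I error follows, and none that power falls to 74%. The case for acting is that the data are already planned for collection and the change is cheap.

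**What to change.** 1. State the look-back of the baseline help-seeking item and reconcile it with the eligibility criteria, or delete the premise. Give the completer restriction a justification of its own or drop it.
2. Make the primary test a logistic model with treatment arm, prior consultation (never / more than 3 months ago / within 3 months) and the baseline GHSQ mental health professional item. Keep the crude proportions and odds ratio as supportive results, and say that the adjusted odds ratio is conditional.
3. Prespecify a fallback, such as merging consultation categories, if one is sparse. At the planned rates, 100 completers per arm yield about 10 + 25 = 35 events for four model terms besides the intercept.
4. Add a sensitivity analysis in participants with no consultation in the 3 months before randomisation.
5. Use the recorded time since first consultation to report, by arm, how many events were first contacts.

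Cost: analysis wording, plus a check that the basic data sheet or the screening call captures the timing of past consultation finely enough for the three categories. No new instrument and no change in sample size. The wording should be settled before the outcome data are analysed; data collection is expected to run to July 2026.

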### Objectives

The objectives of the study are to evaluate the effectiveness of the minimally guided MindNotes app in enhancing professional help-seeking behaviors among individuals with self-reported common mental health concerns and significant psychological distress who are not currently engaged in treatment. Additionally, the study aims to examine the utility of this app in improving the inclination to seek help from mental health professionals, reducing perceived barriers to seeking professional help for mental health, reducing psychological distress, and documenting perceived benefits of using the app. Help-seeking behavior is the primary outcome variable, while help-seeking inclination, barriers to seeking professional help, and psychological distress are the secondary outcome variables.

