#### Overview of Mood Monitoring–Based Intervention

Mood monitoring apps can serve as credible active control conditions because they engage participants in regular self-reflection and emotional tracking without delivering targeted therapeutic content [28]. Moreover, mood tracking has been shown to improve emotional self-awareness and reduce depressive symptoms through increased insight and regulation, making it a psychologically active but nonspecific comparator in this study context involving help-seeking behavior as the primary outcome variable [29].

The participants in the control group will be asked to engage with a mobile-responsive, web-based mood monitoring or mood-logging app for the same 4-week duration as the intervention group. They will be instructed to log their mood at least twice a day for 4 weeks on this mood monitoring app. This would involve rating their mood on a 7-point Likert scale measuring levels of pleasantness and unpleasantness and indicating the nature of their predominant emotion from a list of emotion words provided (eg, happy, guilty, angry, sad, etc). Additionally, they will receive 4 generic reminders to encourage mood tracking and engage in self-care, along with 2 educational messages focused on enhancing mental health awareness via WhatsApp. These messages will include basic and brief information on managing common mental health concerns without any personalized elements. Overall, the mood-logging web app, along with a few educational messages, is expected to serve as an active control by controlling for nonspecific factors such as user engagement, expectancy effects, and digital interaction while offering a credible low-intensity self-help strategy to gain self-awareness.

To summarize, in addition to the opportunity to engage with the respective apps (MindNotes or mood-logging web application), both groups will receive 6 messages through the 4-week period of the study. The intervention group will receive 2 generic reminders alongside 4 personalized professional connect messages. The control group will receive 4 generic reminders and 2 educational cards focused on mood tracking, self-awareness, and emotional well-being. These reminders and messages are strategically distributed throughout the 4-week study period to promote participant engagement with either the MindNotes app or the mood-logging app within a minimal guidance framework, as shown in Table 1.

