Help-seeking behavior from a mental health professional will be assessed at baseline, postintervention assessment, and follow-up through a single yes or no item. If help is sought, details on the nature of professional consultation, duration since first consultation, type of treatment, and satisfaction with consultation will be assessed [27]. If professional consultation for mental health concerns has not been sought since participation in the study, the reasons for not seeking consultation will be explored through an open-ended item.

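### The primary outcome is analysed in completers only, for a reason unrelated to missing data, so randomisation no longer guarantees a fair comparison

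*Protocol article*

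**What the plan says.** The Objectives section states: "Help-seeking behavior is the primary outcome variable". Under Data Collection Instruments, help-seeking from a mental health professional "will be assessed at baseline, postintervention assessment, and follow-up through a single yes or no item". The Procedure section places the postintervention assessment in an online survey and adds: "A follow-up telephonic interview will be conducted 1 month after the postintervention assessment to ascertain help-seeking inclination and help-seeking behavior".

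The Data Analysis Plan compares help-seeking between arms at both post-baseline times by chi-square test and odds ratio. It notes that nobody in this sample is a help-seeker at baseline and concludes that "this will be treated as a completer analysis involving participants who provided postintervention assessment data". The next paragraph analyses the continuous outcomes by linear mixed models under intention to treat, with completer analyses there only exploratory.

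On missing data, the same section plans a chi-square comparison of dropout between arms and a comparison of completers with noncompleters at baseline. It then says: "Sensitivity analyses will be conducted as needed based on the observed pattern of missing data".

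The Power Calculation section says "A sample size of 150 participants per group has been estimated", "allowing for up to 33% attrition commonly observed in minimally guided digital interventions".

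**The concern.** The reason does not lead to the rule. An outcome that is no for everyone at baseline cannot be modelled as change from baseline and offers no baseline value as a covariate. That has no bearing on which randomised participants belong in the comparison; a binary outcome that starts at no can be analysed in all 300. The section is also uneven: the primary outcome gets the population that the authors treat as exploratory for the secondary ones.

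The rule is tied to postintervention data and is written for both time points. Read literally, a participant who skips the survey but answers the 1-month call is excluded although the outcome is known.

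Providing postintervention data happens after randomisation. If it relates to help-seeking, and does so differently in the two arms, the completer comparison is biased. That is plausible here. The trial is unblinded, the outcome is self-reported, and the arms ask for different things. MindNotes users complete one section, explore another and choose the rest, with personalised notes. Of control participants the plan says: "They will be instructed to log their mood at least twice a day for 4 weeks", which is at least 2 × 28 = 56 logs.

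**Working it through.** **1. The plan's own sample size.** Inputs (Power Calculation and Data Analysis Plan): 25% vs 10%, two-sided 5%, 80% power, 33% attrition. With pooled variance and no continuity correction:

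n = [1.960·√(2·0.175·0.825) + 0.842·√(0.25·0.75 + 0.10·0.90)]² / 0.15² = 99.5, so 100 per arm. Then 100/0.67 = 149.3, so 150 per arm.

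The stated 150 is reproduced. The trial is powered on about 100 completers per arm, with up to 50 per arm absent from the primary test.

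**2. What selective completion can do.** The documents give no retention by outcome, so the retention rates below and the common true rate of 15% are assumptions. With q1 = retention of help-seekers and q0 = retention of others:

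completer rate = 0.15·q1 / (0.15·q1 + 0.85·q0)

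The false-positive rate is the exact rejection probability of the uncorrected chi-square test with 100 per arm. Overall retention is about 67% in both arms throughout.

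| Case | MindNotes q1/q0 | Control q1/q0 | Completer rates | False-positive rate |
|---|---|---|---|---|
| Same in both arms | 90%/63% | 90%/63% | 20.1% vs 20.1% | 5.1% |
| Differential, mild | 85%/64% | 67%/67% | 19.0% vs 15.0% | about 12% |
| Differential, one arm | 90%/63% | 67%/67% | 20.1% vs 15.0% | about 16% |
| Differential, opposite directions | 90%/63% | 55%/69% | 20.1% vs 12.3% | about 33% |

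For example, in the mild case 0.1275/(0.1275 + 0.544) = 19.0%. A wider grid has true rates of 10% to 20%, MindNotes help-seekers retained at 80% to 100%, and control loss unrelated to outcome. It gives 7% to 36%.

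**3. Would the planned checks see it?** Dropout is equal in every row, so the comparison of dropout rates shows nothing. The comparison of completers with noncompleters uses baseline variables and cannot observe help-seeking that happens later.

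**4. Would another way of handling missing data see it?** Counting missing as no, with 150 per arm, gives 0.15·q1 in each arm:
- mild case: 12.75% vs 10.05%, false-positive rate 11.3%;
- opposite directions: 13.5% vs 8.25%, false-positive rate 31.0%.

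These are almost the completer figures. In these cases no covariate explains retention, so imputation within arm would reproduce the completer rates.

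**5. What a tipping-point analysis would show.** At the planned rates, completers give 25/100 vs 10/100, p = 0.005. With all 150 per arm and no help-seeking among the missing, 25/150 vs 10/150 gives p = 0.007. Keep the missing MindNotes participants at none and add help-seekers among the 50 missing controls. Three give 13/150 and p = 0.037, four give 14/150 and p = 0.059, and at fifteen the difference is zero.

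**6. Power.**
- 100 completers per arm, 25% vs 10%: 81.6% (exact).
- 150 per arm, missing counted as no, 0.25·0.67 = 16.75% vs 0.10·0.67 = 6.7%: 78.8% (exact).
- 150 per arm, missing in both arms seeking help at 10%, 0.25·0.67 + 0.10·0.33 = 20.05% vs 10%: 68.5% (normal approximation, ignoring imputation variance).

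**The case against.** The strongest reply is that the error rates in step 2 come from chosen cases. This stands. Retention by outcome is assumed, and the 33% case needs help-seekers to stay more in one arm and less in the other. If dropout depends on help-seeking equally in both arms, the error rate is nominal. The figures illustrate a risk and do not estimate it.

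A second reply is that the usual alternatives do no better in those cases. This also stands, as step 4 shows. A reader might infer that 12% to 33% is the price of completers over intention to treat and that imputation would bring it back to 5%. The calculations do not support that: they show the cost of differential, outcome-dependent dropout under either approach.

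Two further inferences go too far. One is that a third of participants are expected to be lost; the Power Calculation section gives an upper planning allowance. The other is that the protection of randomisation is certainly lost; bias needs missingness that relates to outcome differently by arm.

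Third, an article may leave imputation models and sensitivity methods to an analysis plan that is not shown. That is fair for the detail. It does not cover the completer rule or its reason, which the article fixes explicitly, or the wording that makes sensitivity analyses depend on the missing-data pattern seen.

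**Conclusion.** The concern holds. The article fixes a completer set for the primary outcome, and the reason given does not bear on who should be analysed. As worded, the rule also discards outcomes learned only at the 1-month interview. With up to 50 of 150 per arm missing, randomisation no longer guarantees a fair comparison, the planned checks cannot exclude bias, and the choice of sensitivity analyses is left until the missing data have been seen.

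The possible size ranges from none (about 5% false positives) to substantial (about 12% to 33% in the differential cases examined). It rests on an assumed 15% rate in both arms, 67% retention in both, and assumed retention by outcome. The sample size is not in error; it matches the completer analysis.

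**What to change.** Before outcome data are examined, amend the Data Analysis Plan as follows.

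- Define the primary analysis set as all randomised participants, as allocated.
- Use every known outcome, including help-seeking status learned only at the 1-month interview.
- Handle the remaining missing outcomes by multiple imputation, using the stratification factors (age group, gender), baseline K10, the baseline GHSQ item on mental health professionals, prior consultation and app-use data.
- Fix two sensitivity analyses in advance: an arm-specific tipping-point analysis, and one with missing counted as no consultation.
- Keep the completer analysis as supportive.

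The parts do different work. Recovering outcomes at follow-up reduces the bias, and the tipping-point analysis shows how much departure would overturn the result. Imputation and missing-counted-as-no do not by themselves remove bias from outcome-dependent dropout that differs by arm.

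The cost is wording and modest analysis work, using a follow-up interview that is already planned. Power is about 79% with missing counted as no, against about 82% for 100 completers per arm. It could be lower under other assumptions, about 68.5% if the missing in both arms seek help at 10%.
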